##### Adherence

2.6.3.5

The main indicator for adherence to the program will be the number of modules completed. The number of modules completed at the time of T2 divided by the total number of modules and multiplied by 100 will be reported. Furthermore, we will report the number of logins to the platform and the time spent on the platform (in minutes).

### Sample size

2.7

A previous systematic review for digital CBT-I interventions in adults showed effect sizes on various sleep measures ranging from *g* = 0.21–1.09 (Zachariae et al., 2016). A recent systematic review and meta-analysis showed a moderate effect of sleep interventions compared to both active and passive control groups in reducing sleep disturbance in university students, with an SMD of −0.55 [CI: −0.84, −0.26] at post-test (Chandler et al., 2022). However, given our active control condition and pragmatic design, we anticipate a smaller effect size of Cohen's *d* = 0.4.

Sample size calculations for mixed effect models require a number of estimates, or assumptions (Twisk, 2013). We estimate the (within-subject) intraclass correlation coefficient (ICC) of the baseline assessment and three follow-up assessments to be approximately 0.23. A somewhat higher ICC will slightly inflate the minimal detectable effects, a somewhat lower ICC will slightly lower the minimal detectable effects. At a significance threshold of *α* = 0.05 and a power 1-*β* = 0.80, we estimate that a number of 48 participants per group is needed to detect a small to medium effect size of *d* = 0.4. Given the estimated high drop-out rate of 50 % (Zachariae et al., 2016), we plan to include 192 participants in total.

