### Outcome measures

2.6

The outcomes will be evaluated at baseline (T0), 6 weeks (T2), and 18 weeks (T3) after randomization. The T2 measurement is the primary endpoint. Additionally, insomnia severity and the two cognitive mediator variables (DBAS-10 and PSAS) will have an extra assessment point at 3 weeks (T1) after randomization. The questionnaires will be sent out via email and will be filled out in a secured online environment. Participants will be compensated for completing the T2 questionnaires (€15,- voucher) and T3 questionnaires (raffle of eight vouchers of €50,-). Table 2 shows an overview of the assessment instruments used for each time point.

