### Statistical analysis plan

2.8

All statistical analyses will be conducted in the R statistical programming package. All analyses will be performed according to the intention-to-treat approach, meaning all participants who are randomized will be included in the analyses regardless of study completion. Additionally, we will perform a completer-analysis with only those participants who completed the post-test and follow-up assessments, and a dose-response-analysis with adherence to the modules as a predictor of the intervention effect on insomnia severity. We will apply a two-tailed significance level of *α* = 0.05. Assumptions underlying the planned analyses, such as normality and constant variance of residuals, will be checked, reported, and addressed.

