#### Effectiveness analyses

2.8.1

We will fit linear mixed models to examine the primary outcome of change in ISI score between baseline and post-test assessment. We will estimate the effects of time and the interaction between time and group allocation. Due to the repeated measures, the observations are structured hierarchically within the participants. We are primarily interested in the effect of the intervention from baseline to post-test (T0-T2), but we will investigate in several post-hoc analyses whether the effect was maintained between T2 and T3. The independent variable will be group allocation (to either *‘**i-Sleep & BioClock**’* intervention or online psychoeducation) and the dependent variable will be insomnia severity (ISI). We will investigate demographics (e.g. age, sex, year of education, marital status, living situation), baseline severity of symptoms, and stressful life events as covariates, in case of differences at baseline. Clinical significant treatment response from T0-T2 will be reported, defined as reduction in total ISI score of ≥8 points (Morin et al., 2011). Furthermore, we will calculate the effect size Cohen's d by taking the mean difference of the outcomes between intervention and control group and dividing the results by the pooled standard deviations. Cohen's d can be interpreted small <0.2, medium around 0.5, or large >0.8 (Cohen, 1988). For the secondary outcomes (MCTQ, PHQ-9, GAD-7, WSAS, MHQoL and sleep & light diary outcomes), we will follow the same statistical approach as for the primary outcome measure. Negative binominal mixed models will be used for skewed sleep & light exposure diary data with excess zeros (Green, 2021).

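### The 48 per group matches an effect averaged over three follow-ups; for the primary T0-T2 contrast, power at d = 0.4 is about 50-53%, not 80%, at the protocol's own ICC and drop-out

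*Protocol article*

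**What the plan says.** All references are to the protocol article.

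- Section 2.7 (Sample size) sets the effect: "given our active control condition and pragmatic design, we anticipate a smaller effect size of Cohen's" d = 0.4. It puts the within-subject "intraclass correlation coefficient (ICC) of the baseline assessment and three follow-up assessments to be approximately 0.23", with alpha 0.05 and power 0.80. From these, "we estimate that a number of 48 participants per group is needed to detect a small to medium effect size of" 0.4. Drop-out of 50% takes the total to 192.
- The same section adds a sensitivity remark: "A somewhat higher ICC will slightly inflate the minimal detectable effects", and the reverse for a lower ICC.
- Section 2.8 (Statistical analysis plan) makes testing two-tailed and includes everyone randomised.
- Section 2.6 (Outcome measures): "The T2 measurement is the primary endpoint". ISI is also measured at T1 (3 weeks) and T3 (18 weeks). Section 2.6.1 repeats that the main endpoint is at 6 weeks.
- Section 2.8.1 (Effectiveness analyses): "We are primarily interested in the effect of the intervention from baseline to post-test (T0-T2"), from a linear mixed model with time and time-by-group effects. Maintenance from T2 to T3 is left to post-hoc analyses.

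Section 2.7 names neither a formula nor the contrast that it powers.

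**The concern.** An effect averaged over several follow-ups is estimated more precisely than an effect at one visit, because averaging removes part of the within-person noise. If 48 per group depends on that gain, the 80% does not carry over to a single-visit primary contrast. The ICC remark points the same way: its direction is right for an averaged contrast and wrong for a baseline-adjusted or change contrast at T2. At stake is the only power statement in the article. A reader will take it to cover the primary endpoint, and will interpret a non-significant T2 result in that light.

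**Working it through.** **Inputs.** d = 0.4, alpha 0.05, power 0.80, ICC 0.23, 48 evaluable per group and 50% drop-out (section 2.7); two-sided testing (section 2.8); three post-baseline ISI measurements (section 2.6). SD is set to 1. (z_0.975 + z_0.80)² = (1.960 + 0.842)² = 7.849.

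**Step 1: reproduce 48.** For a group difference averaged over T follow-ups,

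n = 2 × 7.849 × [1 + (T − 1) × ICC] / (T × d²).

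- T = 3: 2 × 7.849 × 1.46 / (3 × 0.16) = 47.75, so 48. This matches.
- T = 1: 98.1. T = 2: 60.3. T = 4: 41.5. None of these matches.
- Drop-out: 48 / 0.5 = 96 per group, 192 in total. This matches.

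**Step 2: direction of the ICC effect.** Variance factors, with SD = 1:

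- average of three follow-ups: (1 + 2 × ICC) / 3, which rises with ICC;
- T2 alone: 1, unaffected;
- T2 adjusted for baseline: 1 − ICC², which falls with ICC;
- T0-T2 change: 2 × (1 − ICC), which falls with ICC.

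Only the first agrees with the sentence in section 2.7.

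**Step 3: power at T2 with 48 per group observed there.** Power = Φ(0.4 / √(2v/48) − 1.96).

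- T2 alone, v = 1: 0.4 / 0.2041 = 1.960, power 50%.
- Baseline-adjusted, v = 1 − 0.23² = 0.947: 0.4 / 0.1987 = 2.014, power 52%.
- Detectable d at 80% power, baseline-adjusted: 2.802 × 0.1987 = 0.56.
- Evaluable n for 80% power, baseline-adjusted: 2 × 7.849 × 0.947 / 0.16 = 92.9, so 93 per group.

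**Step 4: mixed model on all 96 randomised per group.** Compound symmetry at ICC 0.23; 48 per group complete, 48 lost by T2, and half of those lost still giving T1 (an assumption). The variance of the T2 group effect comes from the information matrix.

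- Common baseline mean: variance 0.0390, power 53%.
- Separate baseline means: variance 0.0514, power 42%.

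Whether none or all of the drop-outs give T1 hardly matters: 52.1% to 52.8% with a common baseline, 42.0% to 42.4% with separate baselines.

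**Step 5: sensitivity to ICC.** Same loss pattern, common baseline, beside the n that the averaged formula would need:

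| ICC | T2 power | n per group, averaged formula |
|---|---|---|
| 0.23 | 53% | 48 |
| 0.5 | 64% | 66 |
| 0.6 | 71% | 72 |
| 0.7 | 81% | 79 |

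**Step 6: sensitivity to loss, ICC 0.23.** With no loss (96 per group), power is 79% for T2 alone, 81% baseline-adjusted or common-baseline, and 61% with separate baselines. If one third were missing at T2 (illustrative) and 50% only by T3, common-baseline power would be about 65%.

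**The case against.** - **The averaging is inferred.** Section 2.7 prints no formula, and it defines the ICC over four measurements, for which T = 4 gives 42. A one-sided calculation with T = 2 also gives 48. This stands as a caution on wording: the figure is consistent with averaging but not documented as such. The inference is still strong. Testing is two-tailed, there are three follow-ups, the match uses only stated inputs, and the ICC remark agrees independently.
- **The text never ties the 80% to T2.** Correct. But it is the only power claim, and T2 is the only primary endpoint.
- **A reader might put power as low as 35%.** That is the figure for a change score in completers only: v = 1.54, 0.4 / √(2 × 1.54 / 48) = 1.579, power 35%. The documents do not support it as the planned analysis. Section 2.8 includes everyone randomised, and section 2.8.1 lists time and time-by-group without a group main effect, which read literally is the common-baseline model.
- **A reader might say that the calculation requires d = 0.4 already at week 3.** It does not. The averaged formula needs only a mean effect of 0.4 over the follow-ups.
- **The shortfall depends on ICC and on when drop-out occurs.** This stands. Section 2.7 does not say by which visit the 50% applies, and at ICC 0.7 the common-baseline model reaches about 81%. But 0.7 is three times the planning value and would raise the protocol's own requirement to 79 per group. Section 2.7 itself uses the 50% to go from 48 to 96, so 48 observed at T2 is a fair reading.

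**Conclusion.** The concern holds. The calculation in section 2.7, including the direction of its ICC remark, does not fit the T0-T2 contrast that sections 2.6, 2.6.1 and 2.8.1 make primary. At d = 0.4, ICC 0.23 and 50% of T2 scores missing, power is about 50-53% for T2 alone, the baseline-adjusted contrast or the common-baseline mixed model. It is about 42% if the mixed model estimates separate baseline means. The baseline-adjusted detectable effect is about 0.56, not 0.4.

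This rests on three assumptions: the averaging is inferred from an arithmetic match and the ICC sentence; the 50% is taken to apply at T2; and the mixed-model figures assume compound symmetry, with half the drop-outs giving T1. The documents do not support a flat statement that T2 power is this low whatever the ICC and loss. The figures hold at the protocol's own planning values and improve with a higher ICC or better retention.

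**What to change.** Keep N = 192 and rewrite section 2.7:

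1. Attach 80% power at d = 0.4 only to the effect averaged over T1-T3, and name the formula and contrast.
2. For the primary T0-T2 contrast, state power of about 52% (detectable d about 0.56) at ICC 0.23 and 50% loss, with a range over ICC and over T2 loss.
3. Reverse the ICC sentence for the T2 contrast: when baseline is used, a higher ICC lowers the detectable effect.
4. Confirm in section 2.8.1 that the primary mixed model has time and time-by-group terms with no group main effect, so that both arms share one baseline mean. At ICC 0.23 this is worth about 10 points of power over separate baseline means (53% against 42%).

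The cost is wording and a less favourable stated power; no extra participants are needed.

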### Statistical analysis plan

2.8

All statistical analyses will be conducted in the R statistical programming package. All analyses will be performed according to the intention-to-treat approach, meaning all participants who are randomized will be included in the analyses regardless of study completion. Additionally, we will perform a completer-analysis with only those participants who completed the post-test and follow-up assessments, and a dose-response-analysis with adherence to the modules as a predictor of the intervention effect on insomnia severity. We will apply a two-tailed significance level of *α* = 0.05. Assumptions underlying the planned analyses, such as normality and constant variance of residuals, will be checked, reported, and addressed.

#### Effectiveness analyses

2.8.1

We will fit linear mixed models to examine the primary outcome of change in ISI score between baseline and post-test assessment. We will estimate the effects of time and the interaction between time and group allocation. Due to the repeated measures, the observations are structured hierarchically within the participants. We are primarily interested in the effect of the intervention from baseline to post-test (T0-T2), but we will investigate in several post-hoc analyses whether the effect was maintained between T2 and T3. The independent variable will be group allocation (to either *‘**i-Sleep & BioClock**’* intervention or online psychoeducation) and the dependent variable will be insomnia severity (ISI). We will investigate demographics (e.g. age, sex, year of education, marital status, living situation), baseline severity of symptoms, and stressful life events as covariates, in case of differences at baseline. Clinical significant treatment response from T0-T2 will be reported, defined as reduction in total ISI score of ≥8 points (Morin et al., 2011). Furthermore, we will calculate the effect size Cohen's d by taking the mean difference of the outcomes between intervention and control group and dividing the results by the pooled standard deviations. Cohen's d can be interpreted small <0.2, medium around 0.5, or large >0.8 (Cohen, 1988). For the secondary outcomes (MCTQ, PHQ-9, GAD-7, WSAS, MHQoL and sleep & light diary outcomes), we will follow the same statistical approach as for the primary outcome measure. Negative binominal mixed models will be used for skewed sleep & light exposure diary data with excess zeros (Green, 2021).

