### Aims and hypotheses

1.1

The objective of this study is to evaluate the effectiveness of the guided online ‘*i*-*Sleep & BioClock*’ intervention in reducing insomnia in university students compared to an online psychoeducation control program. We hypothesize that the intervention group will show significantly more improvement in insomnia severity (primary outcome) than the control group at post-test, which will be maintained at 18-week follow-up. Similarly, we expect significant improvements in secondary outcomes assessed by the sleep & light exposure diary, depression and anxiety symptoms, functioning, academic performance, and quality of life. Since young adults are more prone to eveningness (Roenneberg et al., 2007), we expect that chronotype will on average shift toward morningness. Additionally, social jetlag is expected to decrease in both groups since fixed bedtimes are recommended.

The secondary aim of this study is to explore potential mediators of the intervention effect. Cognitive mediators, such as pre-sleep arousal and dysfunctional beliefs and attitudes about sleep were found to be mediators of the effect of CBT-I interventions in the adult population, which is why we hypothesize that they will be mediators in the student population too (Lancee et al., 2019; Parsons et al., 2021). Moreover, light exposure, circadian shift, and variability in sleep patterns will be examined as behavioural mediators (Schwartz and Carney, 2012).

The third aim of the study is to investigate potential moderators of treatment response, in order to determine who benefits most of the intervention. We hypothesize that chronotype influences the responsiveness to CBT-I, but not to online psychoeducation since the *‘**i-Sleep & BioClock**’* intervention includes intervention elements specifically targeting the biological clock. Other variables, such as sociodemographic variables and symptom severity, will also be tested as moderators, using tree-based interaction models. Outcome expectations, adherence to the program, and stressful life events are expected to be predictors of treatment response (Constantino et al., 2018; Li et al., 2019).

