#### Primary outcome

2.6.1

The primary outcome will be *insomnia severity*, measured with the Insomnia Severity Index (ISI), which is a reliable and valid instrument, with internal consistency coefficients of *α* = 0.90 in community samples and *α* = 0.91 in clinical samples (Morin et al., 2011). The ISI consists of 7 items with a 5-point Likert scale (0 = not at all, 4 = extremely) and scores range from 0 to 28, with higher scores indicating more severe insomnia. The ISI has been validated for online use (Thorndike et al., 2011). The main endpoint will be at post-test (6 weeks after baseline). Secondary endpoint will be the 18-week follow-up. Participants are treatment remitters if the ISI score at T2 is <10, and treatment responders if there is a reduction in the total ISI score of >8 (Morin et al., 2011).

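### The pre-stated 18-week ISI hypothesis is left to several post-hoc analyses of T2 to T3, which on their plain reading do not show whether the arms differ at 18 weeks

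*Protocol article*

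**What the plan says.** Section 1.1 (Aims and hypotheses) predicts a greater ISI improvement with the intervention at post-test, "which will be maintained at 18-week follow-up". Section 2.6.1 (Primary outcome) puts the main endpoint at 6 weeks and adds: "Secondary endpoint will be the 18-week follow-up". The abstract's objectives name both time points, and the Discussion lists persistence of the effects as part of its secondary aim.

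Section 2.8.1 (Effectiveness analyses) describes a linear mixed model for ISI: "We will estimate the effects of time and the interaction between time and group allocation". The interest is placed on T0 to T2. For the later period the section says only that "we will investigate in several post-hoc analyses whether the effect was maintained between T2 and T3". It does not give the contrast or say what would count as maintained. Section 2.8 sets the error rate: "We will apply a two-tailed significance level of" 0.05.

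**The concern.** The same result has two standings. It is a directional hypothesis and a named endpoint in sections 1.1 and 2.6.1, but the object of a plural, post-hoc exercise in section 2.8.1.

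The interval is also the wrong one for the endpoint. Whether the effect changed between T2 and T3 and whether there is an effect at T3 are different questions. A trial can show no significant T2-T3 change and still have no demonstrable difference at T3. It can also show a significant decline while a worthwhile difference remains.

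If a non-significant change were taken as maintenance, low power would work in favour of the claim: the less precise the test, the easier the claim. What is at stake is the statement about 18 weeks. The primary result at 6 weeks is not affected.

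**Working it through.** **Inputs.** Section 2.7 gives the effect ("we anticipate a smaller effect size of Cohen's *d* = 0.4"), the ICC of the baseline and "three follow-up assessments to be approximately 0.23", 80% power, and the evaluable number ("we estimate that a number of 48 participants per group is needed"), with 50% dropout and 192 in total. Section 2.8 gives two-sided 0.05. ISI is standardised to SD = 1. As an assumption, the stated ICC is used as the T2-T3 correlation r. Because that figure is approximate and covers all assessments, r is also varied from 0.23 to 0.7.

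**Reproducing the plan's figure.** With three follow-ups, n per arm = 2(1.96 + 0.842)² × [1 + 2 × 0.23] / (3 × 0.4²) = 2 × 7.849 × 1.46 / 0.48 = 47.7, so 48. Then 96 / (1 − 0.5) = 192. The formula that returns 48 averages the effect over three follow-ups. It was not set for a T2-T3 change or for T3 alone.

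**T2-T3 change in effect, 48 per arm at both times.** SE = √[2 × 2(1 − r) / 48], and power = Φ(loss / SE − 1.96).
- r = 0.23: SE = √(4 × 0.77 / 48) = 0.253 SD. The 95% CI half-width is 1.96 × 0.253 = 0.50 SD, wider than the whole assumed effect.
- Complete loss (0.4): Φ(1.579 − 1.96) = 35%.
- Loss of half (0.2): Φ(0.790 − 1.96) = 12%.
- r = 0.5: SE = 0.204; 50% and 16%.
- r = 0.7: SE = 0.158; 72% and 24%.

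**96 per arm at T2, 48 at T3, mixed model using all data.** SE = √[(3 − 2r − r²) / 48].

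**No dropout, 96 per arm at both times.** SE = √[4(1 − r) / 96].

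Power against complete loss of 0.4:

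| Data per arm | r = 0.23 | r = 0.5 | r = 0.7 |
|---|---|---|---|
| 48 at T2 and T3 | 35% | 50% | 72% |
| 96 at T2, 48 at T3 | 42% | 55% | 75% |
| 96 at T2 and T3 | 61% | 79% | 95% |

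For 80% power against complete loss, the evaluable number per arm would be 152 (r = 0.23), 99 (r = 0.5) or 59 (r = 0.7).

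**Between-arm contrast at T3, with d = 0.4 fully persisting.**
- T3 scores alone, 48 per arm: Φ(0.4 / √(2 / 48) − 1.96) = 50%. With 96 per arm: 79%.
- Adjusted for baseline at r = 0.23: SE = √[2(1 − 0.23²) / 48] = 0.199, giving 52%. With 96 per arm: 81%.
- Section 2.8.1 lists time and time by group but no separate group term. Read literally, the arms share a baseline mean, and the T0-T3 difference in change is then the baseline-adjusted T3 difference, so the 52% applies. If a group term were added and raw change compared in 48 pairs per arm, power at r = 0.23 would be 35%.

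**The case against.** The strongest objection is that the criticised rule is not in the text. Section 2.8.1 does not name a significance test of T2-T3 change as the only analysis and never says that non-significance will be read as maintenance. A reader might infer that the plan would deliver a maintenance claim by default, but the document does not support that. This part of the objection stands.

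Second, a T3 comparison is not excluded. The objectives name 18 weeks, outcomes are collected at T3, and a mixed model with T3 as a level of time would contain the contrast. Post-hoc may simply mean follow-up contrasts after the main model, since they are announced in advance. That is a fair reading of the word. It does not remove the mismatch: for a hypothesis and endpoint fixed in advance, the one stated route is about T2 to T3.

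Third, a journal article leaves the number and form of such contrasts to a full analysis plan. Agreed, and the missing detail is not the point. The point is the route and label that the article does state.

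Fourth, a reader might conclude that a T2-T3 test would usually miss a complete loss of effect. That holds at the plan's ICC with 48 evaluable per arm, but not across the plausible range. The analysis is by intention to treat, mixed models use partial data, and at higher correlation or better retention the power is well above one half.

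Finally, T2 is the primary endpoint, and the Discussion itself says that long-term conclusions cannot be drawn from the last follow-up. This limits the weight of the point.

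**Conclusion.** The point holds in a limited form. Sections 1.1 and 2.6.1 make the 18-week ISI effect a pre-stated hypothesis and the secondary endpoint, while section 2.8.1 handles it only through post-hoc analyses of T2 to T3. On its plain reading that does not answer whether the arms differ at T3. These two conclusions depend on no numerical assumption.

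The caution against reading non-significance as maintenance has a size that depends on ICC and retention. Power against complete loss of d = 0.4 is 35% on the plan's own inputs and runs up to 95% with full retention and a correlation of 0.7. The finding is neither that the plan commits this misreading nor that the test would fail in every scenario. The change is worth making before analysis. It does not bear on the primary result.

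**What to change.** In section 2.8.1, replace the post-hoc wording with one pre-specified secondary contrast from the same mixed model: the between-arm difference in ISI change from T0 to T3, with its 95% CI, tested at two-sided 0.05 only if the T2 contrast is significant. Claim an effect at 18 weeks only if that CI excludes zero in favour of the intervention. Report the T2-T3 change in effect with its CI as an estimate of how much is retained, and state that maintenance will not be inferred from a non-significant change. A T3 effect shows benefit at 18 weeks, not that all of the T2 benefit was kept, so both figures are needed.

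The cost is a few sentences. T3 ISI is already collected, the time-by-group term is already in the model, and testing T3 only after T2 takes no alpha from the primary endpoint. The downside should be stated openly: with 48 per arm the T3 contrast has only about 50% power even if d = 0.4 fully persists (about 79% with 96 per arm), and the requirement that T2 be significant first can only lower this. Low power then makes the 18-week claim harder to reach, not easier.
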